### Statistical analyses

All analyses will be carried out using STATA® version 17.0 for Mac according to the intention-to-treat (ITT) principle unless specified otherwise. In this study, we defined ITT as the subsample of a person with a baseline assessment and at least one observation on the primary effectiveness outcome measure or the primary health-economic outcome measure.

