### Randomization

Before randomization, the participant will complete the baseline assessment. Then, cluster randomization on the level of the care professionals will be applied. Therefore, professionals and their corresponding set of 1–5 recruited participants will be randomly allocated either to the intervention arm (receives the PiB program in addition to usual care) or to the control arm (only receives usual care) by a spreadsheet random number generator. Because of the shared control arm design, fewer control arm participants need to be recruited than intervention participants. Therefore, in this study, 65% of participants will be allocated to the intervention arm and 35% to the control arm. Stratified randomization [23] will be utilized to ensure that distribution among care professionals within each organization will be as even as possible. Finally, due to variations in the cluster sizes, deviations could occur for the target sample size. In case the allocation diversion is larger than 10% than the desired allocation of 65/35 (e.g., 77% was allocated to the intervention arm at some point during recruitment), the probability to be allocated to the under-allocated arm (e.g., the control arm) will be set to 0.80. The randomization process, enrollment of participants, and assignment of participants to their arms will be executed by the main researcher ([name]). Due to the nature of the intervention in this research, blinding of the participant, care professional, outcome assessor, and data analyst will not be attempted because of pragmatic limitations.

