### Procedure

The informal caregivers in the intervention and control arm will be assessed at five-time points: baseline assessment (T_0_), after 3 months (T_1_), 6 months (T_2_), 12 months (T_3_), and 24 months (T_4_). The informal caregivers will complete all measurements either via an online survey, by paper post, or via a telephone interview with the researcher depending on their preference. An overview of the enrollment and assessment procedure is shown in Table 2. To ensure the quality of the research, several measures are taken to limit missing data during the conduct of the trial based on recommendations by Little and colleagues [26]. An example was limiting the data collection burden and inconvenience for participants in the development and selection of the questionnaires.

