### Sample size

The sample size calculation was based on an earlier short-term effectiveness study of PiB [21] that targeted a similar population and used the CSES as a primary effectiveness outcome measure. With an assumed cluster size of 10 informal caregivers, alpha 0.05, power 0.80, and 25% drop-out at 6 months, the total sample size is 126 participants (with 63 in the control arm and 63 in the intervention arm). However, the sample size will be recalculated based on the CSES after 52 participants have completed their baseline assessment so that the targeted sample size can be adjusted with updated information on the standard deviation.

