#### Part 1: effectiveness

Prior to the analysis, the data will be examined for missing data and described. To verify the randomization procedure, potential differences in the baseline characteristics of the intervention and control arm will be examined using t-tests for continuous variables and the chi-squared (*X*^2^) test for categorical variables. A mixed generalized linear model (GLM) will be fitted to the care management CSES score (dependent variable) based on the recommended model of Bell and colleagues [42]. The model will include the following independent variables: trial arm, time (categorically), and the interaction between the trial arm and time. Time will be treated as a categorical variable because Donohue and Aisen [43] discuss that data from early in the trial has less influence in a categorical time model framework. As PIB is aimed at sustainable effects over a longer period, we are interested in the outcome at the end of the trial. Therefore, we believe this approach fits better than treating time as continuous. A link function and distribution family will be chosen that best fits the data (in terms of normality of residuals and linearity). A random intercept will be employed to acknowledge the hierarchical structure of the data (observations clustered within participants, and participants clustered within professionals). An unstructured covariance matrix for residual errors will be applied. If the p-value related to the intervention coefficient is less than 0.05 (2-sided) the intervention will be considered to have a statistically significant effect on the primary outcome, which would confirm our hypothesis. For this analysis, any missing data will be assumed missing at random (MAR) and handled by the mixed model.

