To handle the uncertainty surrounding the ICUR and the ICER, bootstrapping with 5000 replications will be used to estimate 95% bootstrap intervals around cost and QALY differences. The incremental (difference between control and intervention) outcome (12-month QOL-AD effect, total QALYs, and total costs) will be estimated using a mixed GLM using the outcome as the dependent variable, and trial arm and baseline value (baseline QOL-AD, baseline utility, and baseline 3-month costs, respectively) as independent variables. A random intercept will be employed to acknowledge the hierarchical structure of the data (observations clustered within professionals). Uncertainty surrounding the ICUR and ICER will be graphically presented on a cost-effectiveness plane. A cost-effectiveness acceptability curve will show the probability that the intervention is cost-effective in comparison with usual care for a range of willingness-to-pay values.

Missing data will be handled using the guidance from Faria and colleagues [45]. Any missing follow-up data will be tested for conditionality of observed factors at baseline and missingness status at each observation will be tested for conditionality on observed factors at the previous observation. If missingness is only conditional on baseline factors, baseline missing is limited and missingness is not disaggregated (e.g., mostly all or none of the scales are missing at an observation), it will be handled using inverse probability of censoring weights. If missingness is conditional on previous observation it will be handled using multiple imputations.

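### The set labelled ITT is a subsample whose natural reading requires follow-up after allocation, a modified ITT set at odds with the plan's own missing-data methods

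*Protocol article*

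**What the plan says.** Under Statistical analyses, all analyses are to be run "according to the intention-to-treat (ITT) principle unless specified otherwise". The next sentence gives the operational meaning: "we defined ITT as the subsample of a person with a baseline assessment and at least one observation on the primary effectiveness outcome measure", extended by "or the primary health-economic outcome measure". It does not say when the qualifying observation must occur.

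Four other places bear on how this is read:

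- Randomization: "Before randomization, the participant will complete the baseline assessment".
- Sample size: "the sample size will be recalculated based on the CSES after 52 participants have completed their baseline assessment", so the CSES is part of the baseline assessment. The same section gives 126 participants (63 per arm) and 25% drop-out at 6 months.
- Part 1: effectiveness: "any missing data will be assumed missing at random (MAR) and handled by the mixed model". The model has arm, categorical time and their interaction. No separate baseline covariate is named, and the text does not say whether baseline is one of the time levels.
- Cost-utility and cost-effectiveness analysis: missing follow-up is tested for dependence on earlier factors. If it depends only on baseline factors (and two further conditions hold), "it will be handled using inverse probability of censoring weights". If it depends on the previous observation, multiple imputation is used. Each incremental outcome is adjusted for its own baseline value.

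**The concern.** An ITT set is fixed by randomisation. A set that also asks for an outcome observed after allocation is fixed partly by what happened afterwards, and is normally called modified ITT. The label matters because readers will take the result as a comparison of everyone randomised.

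The definition also sits badly with the methods that follow it. A mixed model under MAR, censoring weights and multiple imputation all correct for early loss by using the baseline data of the people who left. If those people are removed when the analysis set is formed, the weights or imputations represent the retained subsample and not the randomised cohort. In the mixed model, the baseline information that makes MAR credible is discarded.

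The trial is unblinded, and only one arm is asked to complete an 8-to-12-week programme, ending at about the time of the first follow-up at 3 months. Loss that differs by arm is therefore possible, although the article gives no figures on it.

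**Working it through.** **1. What the second condition can mean.** Everyone randomised has a baseline assessment, and that assessment contains the CSES.

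- If a baseline value counts as the observation, the condition excludes only a caregiver whose baseline assessment lacks usable values on the primary outcomes. The Data management section expects some missing items, so the condition is nearly, not wholly, empty. The word subsample then does little work.
- If a post-baseline value is required, membership depends on follow-up. Because of the either/or wording, and because later visits count, only caregivers with no follow-up on either outcome at any visit are removed.

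**2. How many.** The total of 126 cannot be rebuilt from the article, which states no effect size, SD or intracluster correlation. Its drop-out step is consistent with 47 completers per arm: 47/0.75 = 62.7, rounded up to 63. The share with no follow-up at all is not stated. Taking 0% to 25% as an assumed range, with the plan's 6-month drop-out as the upper end:

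- 5%: 126 × 0.05 = 6.3
- 10%: 126 × 0.10 = 12.6
- 15%: 126 × 0.15 = 18.9
- 25%: 126 × 0.25 = 31.5

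So 0 to about 31 caregivers would be removed.

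**3. Effect on the estimate.** The assumptions are a true effect of zero, baseline and one follow-up each with SD 1, correlation ρ of 0.5 or 0.7, and loss that depends on baseline only (MAR). Let Δ be the difference between arms (PiB minus control) in mean baseline among those retained. After deletion:

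- bias of the raw follow-up difference = ρΔ
- bias of the difference in change from baseline = (ρ − 1)Δ
- bias of the baseline-adjusted difference = 0

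The change contrast is what arm-by-time estimates if baseline is a level of time. Loss follows a logistic model in baseline with slope −1 (low scorers leave), 0 or +1 per SD, with the intercept set to give the stated loss.

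| Loss, PiB / control | Slope, PiB / control | Δ | Raw follow-up, ρ = 0.5; 0.7 | Change, ρ = 0.5; 0.7 |
|---|---|---|---|---|
| 15% / 15% | −1 / −1 | 0.000 | 0; 0 | 0; 0 |
| 20% / 10% | −1 / −1 | 0.082 | +0.041; +0.058 | −0.041; −0.025 |
| 20% / 10% | −1 / 0 | 0.173 | +0.087; +0.121 | −0.087; −0.052 |
| 20% / 5% | −1 / +1 | 0.220 | +0.110; +0.154 | −0.110; −0.066 |

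For example, row 3 at ρ = 0.7 gives 0.7 × 0.173 = 0.121 and −0.3 × 0.173 = −0.052. A simulation with 1,000,000 per arm gave the same values to within sampling error. In every scenario a likelihood estimate that kept all randomised caregivers, with baseline as an outcome, stayed within 0.003 of zero.

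**4. Where the definition bites.** In Part 1, keeping baseline-only caregivers helps only if baseline CSES is a level of time. If it is not, they add nothing to the likelihood under either definition. In Part 2, adjustment for the outcome's own baseline value gives zero bias in all the rows above even after deletion. Exposure remains if early loss depends on other baseline factors, which is where the weights or imputation need these people.

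**The case against.** The strongest reply is that the definition never says after allocation. Read with the promise to handle any missing data by the mixed model, it could mean that nobody with a baseline CSES is excluded. That reading is possible, and the requirement for follow-up is an inference. It is the more natural inference, because otherwise the condition has almost nothing to do. On either reading the sentence needs rewording.

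The second reply is that the set is wider than it first looks: an observation on either outcome at any visit keeps a caregiver in. This stands, and it limits the loss to people with no follow-up at all.

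The third concerns direction. A reader might infer that deletion favours PiB. With assumed loss of 15% against 5% and leavers 0.5 SD lower at follow-up, the raw follow-up difference does shift by (0.15 − 0.05) × 0.5 = +0.05 SD. The documents do not support this as the bias of the primary analysis, for three reasons:

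- The loss figures are not in the article.
- If the gap arises through baseline, Δ = 0.05/ρ, and the change contrast shifts by (ρ − 1) × 0.05/ρ. This is −0.05 at ρ = 0.5 and −0.02 at ρ = 0.7, against PiB.
- If leavers resemble stayers at baseline and differ only later, the data are not MAR, and the +0.05 SD remains whichever set is used.

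Finally, to say that the definition breaks the randomised comparison and the weighting goes too far. No arm-specific drop-out is given, and Part 2 already adjusts for the relevant baseline value. This too stands.

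**Conclusion.** The point holds as a fault of definition and labelling with a conditional effect on the results. The article invokes ITT and then defines a set that, on its more natural reading, is modified ITT and conflicts with its own handling of missing data.

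The number removed is unknown, between 0 and about 31 of 126 under an assumed no-follow-up share of 0% to 25%. Bias is about zero when early loss is similar in size and pattern across arms. Under the assumed differential, baseline-dependent loss it is roughly 0.02 to 0.16 SD in absolute size (0.025 to 0.154 in the table, rounded outward), and its sign depends on the contrast. No direction in favour of either arm can be claimed from the documents. Part 2 is at risk mainly if early loss depends on factors beyond the adjusted baseline value. All bias figures rest on assumed loss rates, correlations and MAR with one follow-up, and illustrate scale only.

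**What to change.** - Define ITT as all randomised caregivers, analysed in the arm allocated to their care professional, regardless of follow-up. Apply the same rule to controls taken from the collaborating study once they have been selected by matching.
- In the Part 1 mixed model, state that baseline CSES is a level of time, so that caregivers with baseline only contribute to the likelihood.
- In Part 2, estimate the censoring weights or multiple imputation on this full set.
- Keep the present subsample only as a sensitivity analysis, named modified ITT, and state that its qualifying observation must be post-baseline if that is what is meant.

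The cost is one redefinition, one clarification of the model and one relabelled sensitivity analysis. No additional data are needed. The change does not protect against loss that is not MAR.

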#### Part 1: effectiveness

Prior to the analysis, the data will be examined for missing data and described. To verify the randomization procedure, potential differences in the baseline characteristics of the intervention and control arm will be examined using t-tests for continuous variables and the chi-squared (*X*^2^) test for categorical variables. A mixed generalized linear model (GLM) will be fitted to the care management CSES score (dependent variable) based on the recommended model of Bell and colleagues [42]. The model will include the following independent variables: trial arm, time (categorically), and the interaction between the trial arm and time. Time will be treated as a categorical variable because Donohue and Aisen [43] discuss that data from early in the trial has less influence in a categorical time model framework. As PIB is aimed at sustainable effects over a longer period, we are interested in the outcome at the end of the trial. Therefore, we believe this approach fits better than treating time as continuous. A link function and distribution family will be chosen that best fits the data (in terms of normality of residuals and linearity). A random intercept will be employed to acknowledge the hierarchical structure of the data (observations clustered within participants, and participants clustered within professionals). An unstructured covariance matrix for residual errors will be applied. If the p-value related to the intervention coefficient is less than 0.05 (2-sided) the intervention will be considered to have a statistically significant effect on the primary outcome, which would confirm our hypothesis. For this analysis, any missing data will be assumed missing at random (MAR) and handled by the mixed model.

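### The primary CSES model does not adjust for baseline CSES, so the 12-month comparison is less precise than the data allow

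*Protocol article*

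**What the plan says.** The protocol article, Statistical analyses, Part 1: effectiveness, gives the fixed part of the primary model in closed form: "The model will include the following independent variables: trial arm, time (categorically), and the interaction between the trial arm and time". Random intercepts cover "observations clustered within participants, and participants clustered within professionals", and "An unstructured covariance matrix for residual errors will be applied". The decision rule is: "If the p-value related to the intervention coefficient is less than 0.05 (2-sided) the intervention will be considered to have a statistically significant effect". The text does not identify that coefficient, and it does not say whether T0 is in the outcome vector.

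Baseline CSES is available for every analysis. The Randomization section states: "Before randomization, the participant will complete the baseline assessment". The intention-to-treat definition under Statistical analyses already requires a baseline assessment.

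Two further places bear on the point. The health-economic models in Part 2 use "trial arm and baseline value (baseline QOL-AD, baseline utility, and baseline 3-month costs, respectively) as independent variables". Randomization is stratified by care organization: "Stratified randomization [23] will be utilized to ensure that distribution among care professionals within each organization will be as even as possible".

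**The concern.** The strongest predictor of a caregiver's 12-month self-efficacy score is likely to be the same score at baseline, and the listed model does not condition on it. The model terms are stated, so this is a choice made in the article and not a detail left to a fuller document.

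At stake is the width of the interval, and hence the power, for the primary outcome. The trial is small (126 participants planned) and allows for 25% drop-out. There is also a risk in the wording of the test. If T0 is an outcome and the reference time category, the arm main effect is the baseline difference and not a treatment effect, so an unnamed intervention coefficient could be read as the wrong term.

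**Working it through.** **The plan's own figure.** The Sample size section gives 126 (63 per arm), cluster size 10, alpha 0.05, power 0.80 and 25% drop-out. It gives no effect size, SD, ICC or baseline correlation, so 126 can be neither reproduced nor refuted. Solved backwards: 63 × 0.75 = 47.25 completers per arm; divide by 1 + 9 × ICC to get n; standardized effect d = 2.80 × √(2/n). This gives d = 0.58 at ICC 0, 0.69 at ICC 0.05 and 0.80 at ICC 0.10. None of this says which contrast was powered.

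**Inputs assumed.** r is the correlation between baseline and 12-month CSES: 0.3, 0.5, 0.7. Variances are equal over time. The ICC is 0 or 0.05, with the professional effect constant over time and clusters of equal size.

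**No clustering.** In units of the outcome variance, the 12-month arm contrast has variance proportional to:
- change score (T0 an outcome, free arm means): 2(1-r)
- follow-up level only (T0 not an outcome): 1
- baseline-adjusted: 1-r²

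The ratios are therefore (1-r²)/[2(1-r)] = (1+r)/2 against the change score, and 1-r² against the follow-up level.

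**With clustering.** Let m be the number of caregivers per professional. The correlation between a cluster's baseline mean and its 12-month mean is R = [r + (m-1)ICC] / [1 + (m-1)ICC], and R replaces r in both ratios. Example: m = 10, ICC 0.05, r = 0.3 gives R = 0.75/1.45 = 0.517 and (1+R)/2 = 0.76.

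| Setting | Ratio to | r=0.3 | r=0.5 | r=0.7 |
|---|---|---|---|---|
| ICC 0 | change score | 0.65 | 0.75 | 0.85 |
| ICC 0 | level | 0.91 | 0.75 | 0.51 |
| ICC 0.05, m=3 | change score | 0.68 | 0.77 | 0.86 |
| ICC 0.05, m=3 | level | 0.87 | 0.70 | 0.47 |
| ICC 0.05, m=10 | change score | 0.76 | 0.83 | 0.90 |
| ICC 0.05, m=10 | level | 0.73 | 0.57 | 0.37 |

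Generalized least squares over T0 to T3, comparing a common baseline mean with free arm means and with follow-up only, gives the same values. A covariate model using only each caregiver's own baseline comes slightly short of them: with slope b = r, its ratio to the change score is (1 + b² - 2bR)/[2(1-R)]. At m = 10 this is 0.81, 0.86, 0.92. At m = 3, close to the 1 to 5 caregivers per professional in the Randomization section, it is 0.68, 0.78, 0.86 (0.685, 0.775, 0.865 before rounding), so the shortfall is negligible.

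**In power.** If the unadjusted test has 80% power, adjustment gives Φ(2.80/√ratio - 1.96). At ICC 0 that is 93.5%, 89.9%, 86.0% against the change score, or 83.6%, 89.9%, 97.5% against the level. At ICC 0.05 and m = 10, the change-score ratios give about 90%, 87%, 84%. At r = 0.5 and ICC 0, 126 × 0.75 = 94.5, so about 95 participants carry the information of 126.

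**Organization.** An organization effect that is constant over time cancels from a change contrast, so the gain is 0. On a level contrast the gain is at most organization's share of the variance (a 5% share gives 0.95). As fixed effects in the pooled analysis, organization terms would remove controls from control-only organizations. If 63 intervention participants are the 65%, own controls number 63 × 35/65 ≈ 34, and the variance becomes (1/63 + 1/34)/(2/63) ≈ 1.43 times larger. That breaks even only at an organization share of 1 - 1/1.43 = 30%.

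**The case against.** Arm, categorical time and their interaction is a mainstream repeated-measures model. If T0 is one of its time points, baseline is not ignored. The article also says the model follows a recommended model from a cited source that is not at hand. This stands in part: a reader might infer that baseline data are thrown away, and the article does not support that. The loss is relative to a baseline-adjusted analysis. It remains on both readings of the text.

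A reader might see the baseline covariate in Part 2 as showing that the plan contradicts itself. It does not. Part 2 models one value per person (12-month QOL-AD, total QALYs, total costs), where baseline can enter only as a covariate. Part 1 has repeated measures, where T0 can enter as a time point.

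A reader might infer from the stratified randomization that leaving organization out costs precision or spoils the standard error. Neither is shown. The professional intercept already carries much of the between-organization variance, and ignoring a stratum usually makes a standard error conservative.

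The strongest objection concerns the controls. Some are matched from the collaborating study and, as the Discussion says, come through a different type of organization. With a baseline gap D0 between arms, the adjusted and change estimates differ by (1-r) × D0. Change scores are unbiased under parallel trends; adjustment is unbiased only if conditioning on baseline removes the source difference. This stands in full: adjustment cannot be presented as a cure for selection bias.

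**Conclusion.** The point holds as a matter of precision. The primary model as listed gives up between 15% and 35% of the variance of the 12-month contrast if T0 is an outcome with free arm means, and between 9% and 49% if it is not (r from 0.3 to 0.7, ICC 0). With ICC 0.05 and clusters of ten, the change-score loss shrinks to between 10% and 24%. These ranges rest on assumed correlations and ICCs, because the article gives none, and on equal variances over time. No assumed value favors the listed model.

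No bias or inflated type I error from omitting baseline is demonstrated. This is an improvement the trial should make, not an error that invalidates the analysis. The organization stratum is secondary.

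**What to change.** - Model CSES at T1 to T3, with baseline CSES and its interaction with time as covariates alongside arm, time and arm by time. Keep the professional and participant levels.
- Name the adjusted arm contrast at 12 months (T3) as the single primary test, replacing the unnamed intervention coefficient.
- Prefer the covariate form to forcing a common baseline mean across arms. The common mean relies on randomization, which the matched controls did not have.
- Report the unadjusted 12-month change contrast as a sensitivity analysis, and discuss any gap between the two results in light of the baseline difference.
- State how the organization stratum is handled, and avoid organization fixed effects in the pooled analysis.

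The cost is a change of wording before the analysis. Baseline CSES is already collected before randomization, and the analysis set already requires a baseline assessment, so almost no participant should be lost.

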#### Part 1: effectiveness

The primary objective is to estimate the effectiveness of the blended care program PiB compared to usual care over 12 months. We hypothesize that the care management self-efficacy in terms of CSES of caregivers who receive PiB will have a significantly better self-efficacy than that of caregivers who only receive usual care. The secondary objective is to explore the effect of PiB on the primary outcome care management self-efficacy at 24-month follow-up and on the secondary outcomes: perseverance time, quality of life, service-use self-efficacy, positive experiences related to informed care, experienced care burden, anxiety, caregiver gains, and depression up to 24-month follow-up.

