## Methods/design

A pragmatic, cluster RCT design will be used to study participants’ longitudinal outcomes at baseline (T_0_), at 3 months (T_1_), 6 months (T_2_), and 12 months (T_3_) follow-up, and partly at the 24-month follow-up (T_4_), in the control and intervention arm. The control arm will be shared with another collaborating study (called “Eerder-Erbij”) at the Vrije Universiteit of Amsterdam (the Netherlands). Concretely, this entails that the two studies share their recruitment efforts by each supplying part of the targeted control arm participants but recruit their own intervention arm participants to compare their respective interventions to the shared control arm. The collaborating study will apply the same inclusion criteria, same study procedures, and evaluate the same outcomes over time. See Fig. 1 for the participant's flow diagram of the research. This study protocol follows the Standard Protocol Items: Recommendations for Interventional Trials (SPIRIT) guidelines [22] (see Additional file 1).

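### The primary success rule tests an unspecified intervention coefficient in a model with arm-by-time terms; under the most natural coding that coefficient is the pre-randomization baseline difference, not the 12-month effect

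*Protocol article*

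**What the plan says.** Under Statistical analyses, Part 1: effectiveness, the protocol article fits a mixed generalized linear model to the care management CSES score itself, not to change from baseline. The independent variables are "trial arm, time (categorically), and the interaction between the trial arm and time". No baseline CSES covariate is listed. The decision rule is: "If the p-value related to the intervention coefficient is less than 0.05 (2-sided) the intervention will be considered to have a statistically significant effect". The article adds that meeting this rule would confirm the hypothesis.

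The same paragraph explains the choice of categorical time by saying that "we are interested in the outcome at the end of the trial". Under Objectives, Part 1: effectiveness, the target is 12 months: "The primary objective is to estimate the effectiveness of the blended care program PiB compared to usual care over 12 months". The CSES at 24 months is placed there under the secondary, exploratory objective.

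Methods/design lists assessments at baseline, 3, 6 and 12 months, and partly at 24 months. The Randomization section has the baseline assessment completed before allocation.

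**The concern.** The rule speaks of one intervention coefficient, but the model has an arm term plus one arm-by-time term for each non-reference time. The arm term is the difference between arms at the reference time only. If that time is T0, the rule tests a quantity that PiB cannot have affected. The effect of PiB lies in the arm-by-time terms, which the rule does not name.

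The rule decides the primary hypothesis. Followed literally under that coding, a trial of an effective program would usually be declared negative, and a positive result would reflect imbalance at baseline. The shared control arm adds to this. The Discussion expects participants from the collaborating study to be a somewhat different selection, and the Matching section does not list baseline CSES among its variables. A baseline difference could therefore arise from selection, and the rule would credit it to PiB.

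**Working it through.** **1. What the arm coefficient is.** Write the mean for arm A (1 = PiB, 0 = control) at time t, with r the reference time:

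E[Y] = b0 + b1·A + Σ(t≠r) g_t + Σ(t≠r) d_t·A

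Let D_t be the PiB-minus-control difference in means at time t. Then b1 = D_r and d_t = D_t − D_r.

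| Coding | Arm coefficient b1 | Answers the 12-month objective? |
|---|---|---|
| T0 in outcome, reference T0 | D_0, before randomization | No |
| T0 left out, reference T1 | D_1, at 3 months | No |
| Reference T3 | D_3, at 12 months | Yes |
| Term read as arm-by-T3, reference T0 | not b1 but d_3 = D_3 − D_0 | Yes |

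**2. Which coding the text suggests.** The outcome is the score, CSES is measured at T0, and no baseline covariate is listed. By contrast, the incremental-outcome model in Part 2 (Cost-utility and cost-effectiveness analysis) does name the baseline value as a covariate. T0 as an outcome row, and as the first and hence default reference level, is therefore the most natural reading of Part 1. The article does not state it.

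**3. The plan's own sample size, to set a scale.** The article gives 126 participants (63 per arm), power 0.80, alpha 0.05 and 25% drop-out. Effect size, SD and ICC are not given, so 126 can only be inverted. The drop-out step is consistent: 63 × 0.75 = 47.25 evaluable per arm, and 47/0.75 = 62.7, which rounds up to 63. The implied standardized difference is (1.960 + 0.842) × √(2·DE/47.25), with DE = 1 + (10 − 1)·ICC for the assumed cluster size of 10:

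- ICC 0: DE 1.00, difference 0.58
- ICC 0.02: DE 1.18, difference 0.63
- ICC 0.05: DE 1.45, difference 0.69
- ICC 0.10: DE 1.90, difference 0.80

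**4. Rejection rates by simulation.** There were 300 trials per scenario with 63 per arm, T0 to T3 and about 25% monotone drop-out by T2. Assumptions: total SD 1, within-person correlation 0.5, ICC 0.02, clusters of 3, the same effect at every follow-up, and no true baseline difference. The fitted model had a participant random intercept only, which is simpler than the planned one.

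| Test | Effect 0 | 0.5 SD | 0.58 SD | 1.0 SD |
|---|---|---|---|---|
| Arm, reference T0 | 0.047 | 0.040 | 0.053 | 0.040 |
| Arm-by-T3, reference T0 | 0.043 | 0.650 | 0.813 | 1.000 |
| Arm, reference T3 | 0.040 | 0.670 | 0.823 | 0.997 |
| Arm, T0 left out, reference T1 | 0.027 | 0.767 | 0.877 | 0.997 |

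The Monte Carlo standard error is √(0.05 × 0.95/300) = 0.013 near 5% and √(0.81 × 0.19/300) = 0.023 near 81%. The first row is therefore flat at alpha. In every trial the arm coefficient with reference T0 equaled the raw baseline mean difference to about 1e-15.

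A second simulation was closer to the planned covariance structure: a professional random intercept, unstructured covariance at T0 and T3, 42 professionals with 1 to 5 caregivers, a 0.6 SD effect, no drop-out and 1,500 runs. The arm coefficient rejected in 4.5% of trials and arm-by-T3 in 93%. The 93% is optimistic because no drop-out was applied.

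**The case against.** The strongest reply is that the article never says T0 is an outcome row, never fixes T0 as the reference, and does not say that the intervention coefficient is the arm main effect. That is correct. A reader might infer that the rule cannot detect a PiB effect at all. The text does not support this, because with a 12-month reference, or with the term read as arm-by-T3, the rule detects an effect about as often as one would wish (0.823 and 0.813 at 0.58 SD). The model is also said to follow a cited recommendation, which may settle how baseline is handled but is not available here.

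A second reply is that naming the exact contrast is usually left to the analysis plan. That would answer an omission. Here the article states a rule and ties it to confirming the primary hypothesis, so an analysis plan would have to reinterpret that sentence.

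Three further inferences are tempting and should not be drawn:

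- **The end of the trial means 24 months.** Follow-up does run to 24 months, but the Part 2 costing text treats 12 months as the last follow-up measure, and the 24-month CSES is exploratory. The phrase is ambiguous, not contradictory.
- **The sample size targets 6 months.** Six months appears there only with the drop-out assumption.
- **Type I error is inflated by picking among several interaction terms.** The rule names one coefficient, and nothing permits success on any of several.

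**Conclusion.** The concern holds in this form: the success rule does not identify the contrast to be tested, and two of the plausible codings give an answer to a different question. Under the most natural one, the test is of the pre-randomization difference and rejects at about 5% whatever PiB does. With T0 left out and T1 as reference, it is a test of the 3-month effect. The two readings that fit the 12-month objective are not stated.

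The algebra in step 1 does not depend on effect size, variance or ICC. With unequal clusters and a professional random intercept, the estimate becomes a weighted baseline difference, but the quantity tested is the same. The flat 5% also assumes no true baseline difference; if the borrowed controls differ at T0, the rate would be higher without any PiB effect. The power figures for the 12-month tests rest on the assumptions in step 4.

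Because the rule governs the primary conclusion, it should be corrected before the primary analysis.

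**What to change.** - State whether the T0 CSES is an outcome level or a covariate.
- Replace the rule with one two-sided 0.05 test of the 12-month effect. If T0 is an outcome level, test the arm-by-T3 term with T0 as reference, which is the difference in change from baseline to 12 months. If T0 is a covariate, test the baseline-adjusted arm difference at T3. The sentence should say which, since an unadjusted 12-month difference is a different estimand when the arms differ at baseline.
- Make the T1, T2 and T4 contrasts secondary.
- Change the reference to the end of the trial to 12 months, to agree with the primary objective.

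The cost is a few sentences in the protocol and the analysis plan. No extra data, participants or visits are needed.
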